## Abstract

**Background:**

Non-alcoholic steatohepatitis (NASH) is frequently associated with obesity, and its standard treatment is weight loss with diet and exercise; a dy% weight reduction has been associated with improvement in liver histological and analytical abnormalities. However, less than 25% of subjects achieve this goal. Laparoscopic sleeve gastrectomy (LSG) represents the most common procedure of bariatric surgery, providing effective weight loss and improvement in comorbidities such as NASH, but it is associated with several postoperative complications. Endoscopic bariatric techniques are currently on the rise as a new tool in the fight against obesity, offering patients an alternative to more invasive surgery. However, their efficacy and safety compared with LSG is unclear.

**Methods:**

The TESLA-NASH study is a randomized, controlled, open-label, unicentric clinical trial with a medical device. The aim of this study is to evaluate and compare the efficacy and safety of endoscopic sleeve gastroplasty (ESG) versus laparoscopic sleeve gastrectomy (LSG) in liver histology improvement of patients with obesity +/− metabolic syndrome and NASH. A total of 30 patients will be randomized 1:1 to the experimental or control group.

**Discussion:**

LSG is an effective treatment for weight reduction and for the remission of hepatic alterations. However, LSG is associated with acute and chronic postoperative complications. Bariatric endoscopic techniques promise less invasive and more cost-effective approaches to the treatment of obesity and metabolic comorbidities. ESG represents one of the most promising novel endoscopic interventions and it is mainly proposed for patients with mild-to-moderate obesity, but there are still no guidelines that specify its applicability criteria. This clinical trial will help us apply different tactics to the treatment of obesity and NASH.

**Trial registration:**

ClinicalTrials.gov NCT04060368. Registered on Nov 15, 2019.

## Introduction {6a}

Non-alcoholic fatty liver disease (NAFLD) includes a wide spectrum of hepatic affectation characterized by fat accumulation on the hepatic cells, not attributable to other causes as alcohol or/and certain drugs. Non-alcoholic fatty liver disease (NAFLD) is the most common liver disease worldwide. Its 35 prevalence is estimated between 25 and 40% of adults and its incidence is growing, probably as a 36 result of the increase in obesity and associated metabolic disorders [1]. NAFLD includes a spectrum of 37 pathological situations, ranging from simple steatosis to non-alcoholic steatohepatitis (NASH), and 38 fibrosis and cirrhosis. The later conditions potentially lead to hepatocellular carcinoma (HCC) [2, 3].^.^

At present, NAFLD has turned into the first cause of liver disease in Western countries, with a prevalence of about 30% in the general population [4], due to the current epidemic of obesity and metabolic syndrome. The association is especially strong in morbidly obese patients (BMI greater than 40 kg/m^2^), where more than 90% of present NAFLD, a third of them in the form of NASH, and up to 5–10% of the subjects with progression to cirrhosis [5, 6]. In patients with diabetes mellitus, the prevalence of NAFLD is estimated at 40–70% and NASH at around 22% [7, 8]. In addition, the presence of insulin resistance is related to the severity of liver injury, and the presence of steatohepatitis, cirrhosis, and even the development of complications such as hepatic carcinoma [9]. Dyslipidemia is also frequent in these patients, fundamentally in the form of hypertriglyceridemia and low levels of HDL cholesterol [10, 11]. Overall, 80% of patients present with one of the cardiovascular risk factors that constitute the metabolic syndrome (insulin resistance, obesity, dyslipidemia, and high blood pressure) [12].

The first-line treatment for NASH is the modification of dietary habits and physical activity promoting the loss of weight. A loss of between 3 and 5% of the corporal weight improves steatosis, while to reduce necroinflammatory processes, a weight of at least 10% is needed. The diet must be hypocaloric and individualized [13]. Low-fat diets are recommended in patients with dyslipidemia and low carbohydrate diets for patients with resistance to insulin. Nevertheless, only 25% of subjects reach the target of a loss of weight among 5–10%.

On the other hand, physical activity comprised of aerobic to 1 year [14, 15] improves the hepatic histology of an independent way to the loss ponderal.

Bariatric surgery (BS) is a very effective treatment to induce the loss of weight in subjects with morbid obesity; in fact, surgical procedures are clearly superior to physical exercise and the diet in long-term weight control [16, 17]. Clinical evidences suggest that bariatric surgery in obese patients with NASH can improve all its histological components, including steatosis, inflammation, and fibrosis [18, 19]. Lassailly et al. [18] demonstrated that 1 year after surgery, resolution of NASH occurred in 85% of the patients.

The efficacy of the bariatric surgery on the NASH has been assessed in several previous studies [20–31]; however, these findings have been limited by the large heterogeneity observed in populations and size of the studies. A metaanalysis [32] carried out on 15 studies including 766 patients with hepatic pared biopsies, demonstrated that the steatosis was improved in 91.6% of the patients, the NASH in 81.3% of patients, and the fibrosis in 65.5% of the patients. The global result of these studies also demonstrated that the BS is capable of normalizing the hepatic biomarkers and of improving the histological alterations in patients with NASH, although in some isolated studies there has been observed a minimal progression of fibrosis [29–31].

Nevertheless, in spite of these benefits, a 2010 Cochrane revision suggested that the evidence was insufficient to evaluate the results of the surgery as an option of treatment in patients with NASH [33]. In the same way, a metaanalysis of 2015 suggests that improves the hepatic histology and diminishes hepatic biomarkers, but it also concludes major quality evidences must take place before coming to convincing conclusions on the benefits of the bariatric surgery for the NAFLD [34].

Regarding the safety of BS in patients with NASH, a wide study carried out on the American Nationwide Inpatient Sample demonstrated that the BS collaborates to a global decrease in the mortality of the patients with NASH [35, 36]. But, despite its beneficial effects, complications can arise. Cholelithiasis represents the most common post-surgical complication, which happens in almost one of every three patients bearing cholecystectomies in a higher proportion than the general population which is associated with higher complications after surgeries, prolongation of hospitalizations, and higher mortality rate.

Therefore, although the facts suggest that the bariatric surgery is useful in patients with NASH, this pathology does not constitute at this moment an established indication for the surgery taking into account that there do not exist randomized clinical trials to evaluate the resolution of NASH as a primary objective with this procedure.

At present, the bariatric endoscopy (BE) has emerged as a new therapeutic option for the treatment of obesity in patients who do not have a surgical indication, refuse it or do not comply with conventional treatments. The OverStitch system (Apollo method) demonstrated in 2013 that the use of this technique was sure and feasible in a pilot study with four patients [37]. Later, a study with 20 patients demonstrated a weight loss in 30% of the patients after 6 months [38].

Experience with the BE is, at the moment, scarce. However, the preliminary results are very good [39]. The development of the Apollo method is new, but it has showed adequate without significant adverse events, discharging the first day after the procedure, with good results in multicenter studies and showing significant weight loss during the first 2 years. Most of the weight loss takes place during the first 6 months after the procedure, and the weight loss is maintained or increased at months 12 and 24 [40]. Even though BE works well across the spectrum of obesity, including subjects with BMI over 40, the duration of the long-term effect is still unknown. Patients who undergo this procedure achieve significant improvement in the high blood pressure (HBP), cholesterol, and HbA1C levels control as well as improved liver function tests and an improvement in their obstructive sleep apnea disorder [40]

### Objectives {7}

#### Hypotheses

In patients with non-alcoholic steatohepatitis (NASH) and obesity, ESG will achieve weight loss and improvement in metabolic comorbidities and liver histology equal to or greater than LSD with a lower rate of adverse effects.

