#### Objective

The objective is to evaluate the efficacy of ESG + lifestyle modification versus LSG + lifestyle modification in resolving NASH without worsening of fibrosis.

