##### Sample size {14}

Previous studies have shown a resolution of NASH in the 85% of patients undergoing a bariatric surgery (69.6% in gastric tubing surgery) and a resolution of 25% in patients with a lifestyle intervention. A bilateral ratio comparison test was used for sample size calculation with a confidence level of 99%, a statistical power of 90%, and an assumption of 7% loss. Obtained sample to observe differences is *n*=30 (15 per treatment arm).

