### Statistical methods

#### Statistical methods for primary and secondary outcomes {20a}

Data will be analyzed using SPSS version 19. A descriptive baseline and end-of-follow-up analysis (week 96) of the data will be performed using the mean and standard deviation or the median and range where appropriate for quantitative data and percentage for qualitative data. Quantitative variables will be compared with Student’s *t* test and qualitative variables will be compared with *X*^2^. When variables do not follow a normal distribution, non-parametric tests should be used. Paired data tests will be used to analyze baseline and 96-week results.

All changes in efficacy parameters endpoints will be analyzed in an intention-to-treat and per-protocol analysis and grouped by randomized treatment.

The Intent-to-Treat (ITT) population will include all subjects randomized to treatment. The per-protocol (PP) population will be a subset of the ITT population, excluding subjects that violate key protocol criteria, with the exact list of exclusion reasons to be included in the statistical analysis plan (SAP).

The primary efficacy endpoint, by histopathological improvement of fibrosis by at least 1 stage without any worsening of NASH, and histopathological resolution of NASH without any worsening of the stage of fibrosis will be conducted on the intention-to-treat (ITT) population; so all randomized subjects will be included in the primary analysis.

Secondary endpoints analyzed by descriptive statistics and inferential statistics will include ANOVA. Non-parametric tests may be utilized such as Wilcoxon rank-sum.

For all tests, we will use 2-sided *p* values with alpha < 0.05 level of significance.

All safety variables (i.e., adverse events, laboratory data, vital signs, and ECG) will be summarized by treatment for all patients of the safety set. Descriptive statistics using appropriate summary statistics will be calculated for quantitative safety data as well as for the difference to baseline, when appropriate. In addition, a shift table describing out-of-normal range shifts will be provided for clinical laboratory results.

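### The hypothesis that ESG is at least as good as LSG is of non-inferiority type, but the trial is sized and analysed only with two-sided difference tests and no margin, so the equality half cannot be supported

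*Protocol article*

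**What the plan says.** Under Hypotheses (Objectives {7}), the protocol article expects ESG to give weight loss and "improvement in metabolic comorbidities and liver histology equal to or greater than LSD with a lower rate of adverse effects". The comparator is printed as LSD; from context it is LSG. The Objective that follows is neutral in direction: to "evaluate the efficacy of ESG + lifestyle modification versus LSG + lifestyle modification in resolving NASH without worsening of fibrosis".

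Sample size {14} states that "A bilateral ratio comparison test was used for sample size calculation", at 99% confidence, 90% power and 7% loss. It cites NASH resolution of 85% after bariatric surgery (69.6% after gastric tubing surgery) and 25% with lifestyle intervention. It describes the result in difference terms, "Obtained sample to observe differences is" 30, or 15 per arm.

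Statistical methods {20a} assigns the chi-square test to qualitative variables and sets two-sided p "values with alpha < 0.05 level of significance" for all tests. Efficacy endpoints are to be analysed by intention to treat (ITT) and per protocol (PP), with ITT primary. The article contains no non-inferiority or equivalence label, no margin, and no rule based on a confidence interval.

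**The concern.** Similar or better efficacy with less harm is the logic of a non-inferiority trial. Supporting it means ruling out a deficit larger than some stated amount. A two-sided difference test addresses another question, whether the data are incompatible with no difference. Rejection in favour of ESG would support the superior half of the hypothesis. Failure to reject supports nothing, because a small trial often fails to reject when a large difference exists.

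The plan therefore has no step by which the equality half could be confirmed. The Discussion presents this as the first randomised comparison of a bariatric endoscopic procedure with bariatric surgery in this population, so an unsupported conclusion of equality could carry weight.

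**Working it through.** **Inputs.** From Sample size {14}: surgery rates 85% and 69.6%, lifestyle rate 25%, two-sided alpha 0.01, power 90%, loss 7%, 15 per arm. From Statistical methods {20a}: chi-square, two-sided alpha 0.05. No margin is given, so the margins below are assumptions. Both surgery rates are carried through: 69.6% is the rate given for gastric tubing, while 85% is the one that reproduces the stated sample size. All rates refer to resolution of NASH.

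**Step 1: reproduce the stated sample size.** For a two-sided difference of two proportions with unpooled variance, 85% against 25%:

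n = (2.576 + 1.282)² × (0.85×0.15 + 0.25×0.75) / 0.60² = 14.88 × 0.315 / 0.36 = 13.02, rounded up to 14 per arm.

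With loss added as 14 × 1.07 = 14.98, this gives 15 per arm, 30 in total. (Dividing by 0.93 gives 15.05, so 16 per arm.) With 69.6% against 25% the same formula gives 30 per arm before loss. The stated 30 is thus a difference-test sample size, and no margin entered it.

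**Step 2: probability that the planned test is non-significant.** Exact enumeration over all outcomes of two binomials with 15 per arm, Pearson chi-square without continuity correction, critical value 3.84:

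| True ESG rate | LSG 69.6% | LSG 85% |
|---|---|---|
| 20 points below LSG | 81% | 75% |
| 30 points below LSG | 63% | 54% |
| 25% (the lifestyle rate) | 30% | 5.5% |

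An example: 10/15 resolved on LSG and 5/15 on ESG is an observed deficit of 33 points. The pooled proportion is 15/30 = 0.5, so chi-square = (0.333)² / (0.5×0.5×2/15) = 3.33, which is below 3.84 and so non-significant.

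**Step 3: precision when the rates are truly equal.** Half-width of the 95% interval for the difference = 1.96 × √(2p(1−p)/15):

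- p = 0.696: 1.96 × √(2×0.696×0.304/15) = 0.329, about 33 points.
- p = 0.85: 1.96 × √(2×0.85×0.15/15) = 0.256, about 26 points.

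These are normal approximations, rough at this size but adequate for scale.

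**Step 4: what ruling out a deficit would take.** Assumed margin 20 points, one-sided 0.025, 80% power, equal true rates, n per arm = (1.96 + 0.842)² × 2p(1−p) / 0.20²:

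- p = 0.696: 83.03, rounded up to 84 per arm.
- p = 0.85: 50.04, rounded up to 51 per arm.

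Both are before loss. With 15 per arm, power to exclude a 20-point deficit is about 22% (69.6%) or 34% (85%). The smallest margin testable with 90% power is about 54 points (69.6%) or 42 points (85%).

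**The case against.** The strongest reply is that the conflict lies in one loosely worded sentence. The Objective and Trial design sections compare ESG with LSG without stating a direction, nothing calls the trial non-inferiority or equivalence, and the data monitoring section speaks of obtaining first results. A two-sided comparison fits all of that. The statistical analysis plan, which the article mentions but which is not shown, might hold an interpretation rule and the interval method. This stands in part: the neutral Objective makes rewording the natural remedy, and the choice of interval method can be left to the analysis plan. It does not remove the mismatch, because the article has already fixed the sample size as a difference test, and no later document can make 15 per arm adequate for an ordinary margin.

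Three stronger readings are tempting and are not supported:

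- A reader might infer that p > 0.05 will be reported as equality. The article nowhere says how a non-significant result will be interpreted.
- A reader might infer that the trial would very likely return non-significance even if ESG were far worse. That depends on the rates: with ESG at 25% the test misses the difference about 30% of the time (LSG 69.6%) or 5.5% (LSG 85%). The high probabilities belong to deficits nearer 20 points.
- A reader might infer that a primary ITT analysis biases the trial towards equality. Both procedures are single interventions, no crossover or non-adherence rate is given, and the direction of any bias depends on how missing biopsies are handled. A per-protocol analysis of efficacy is already planned.

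**Conclusion.** The concern holds as a mismatch between stated parts of the plan. The hypothesis is of non-inferiority type; the sample size and tests are for difference, with no margin or interval rule. The analysis can support superiority of either arm, but not equality, and a non-significant result would be uninformative on that point. A true 20-point deficit would go undetected about three times in four (LSG 85%) to four times in five (LSG 69.6%), and a 30-point deficit in rather more than half of trials at either rate.

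The sizes rest on the two surgery rates in the article, 15 evaluable patients per arm (losses would make matters worse), the uncorrected chi-square test, and an assumed 20-point margin where a margin is used. The mismatch itself depends on none of these.

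**What to change.** 1. Reword the efficacy hypothesis as estimation of the ESG-minus-LSG difference in histological response.
2. Make the primary result the risk difference with a two-sided 95% confidence interval, in the ITT set and in the PP set already planned. An interval suited to small samples, such as Newcombe or Miettinen-Nurminen, can be named in the analysis plan.
3. State that p > 0.05 will not be interpreted as equality.
4. Permit a claim that ESG is at least as good as LSG only if the lower confidence limit excludes a margin justified and fixed in advance. If that claim is to be the aim of the trial, the sample size must be recalculated for the margin.

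Items 1 to 3 change wording and reporting only; enrolment, conduct and data collection are unaffected. The cost is a more modest claim: at equal true rates the interval would still reach about 26 to 33 points below zero.

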#### Objective

The objective is to evaluate the efficacy of ESG + lifestyle modification versus LSG + lifestyle modification in resolving NASH without worsening of fibrosis.

#### Trial design {8}

The TESLA-NASH study is a randomized, controlled, open-label, unicentric clinical trial with a sanitary product, designed to evaluate the efficacy of two gastric techniques (endoscopic versus laparoscopic) in the resolution of NASH without worsening liver fibrosis.
Experimental group: ESG + lifestyle modificationsControl group: LSG + lifestyle modifications

A total of 30 eligible participants will be randomly assigned (stratified by the presence or absence of type II diabetes mellitus) to the experimental group or the control group with a 1:1 ratio. The participants will be recruited at the Hospital Marqués de Valdecilla from June 2020 to June 2021.

## Methods: participants, interventions, and outcomes

### Study setting {9}

The study will be performed in the Hospital Marqués de Valdecilla, a third-level hospital located in the north of Spain. The Clinical Trials agency and SCReN were responsible for obtaining authorization from the local ethics committee (EC) and notifying the Spanish Agency of Medicines and Medical Devices of the start-up of the study. The study was approved by the Ethical Committee of Cantabria.

### Eligibility criteria {10}

The patient selection will be carried out by the gastroenterologist at daily check-ups. The informed consent will be signed by patients before their inclusion in the study. Patients must present obesity associated or not to a metabolic syndrome according to the criteria of NCEP ATP III, and a NASH diagnosis according to the histological parameters.

#### Inclusion criteria

Subjects between the ages of 18 and 60 (inclusive) at the time of signing the informed consent form.They must provide a signed written informed consent and agree to comply with the study protocol.BMI ≥35–45 kg/m^2^ and ≤30–35 kg/m^2^ associated or not with metabolic risk factors (diabetes mellitus, hypertension, dyslipidemia), and subjects with a BMI ≥30–34.9 and ≤45 kg/m^2^ if type 2 diabetes mellitus is associated.Histological confirmation of steatohepatitis in a diagnostic liver biopsy (biopsy obtained in 6 months prior to randomization or during the screening period) with the following:
NAS score ≥ 4 with ≥1 point for each component.Degree of fibrosis < 4 according to the NASH CRN staging system.For patients with fibrosis ≤ 1, at least one of the following characteristics must be associated:
Metabolic syndrome (NCEP ATP III definition)Type II diabetes mellitus.HOMA-IR > 6Absence of other causes of chronic liver disease (alcoholic, viral, autoimmune, cholestatic disease, Wilson’s disease, α1AT deficit, hemochromatosis)Subject must agree to undergo a liver biopsy 96 weeks after the endoscopic or surgical procedure.

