### Outcomes {12}

#### Primary outcome

Assessment of the efficacy of endoscopic vertical gastroplasty + lifestyle modification against laparoscopic vertical gastrectomy + lifestyle modification in the histological improvement of NASH from baseline to week 96 by the following:
Improvement of fibrosis in at least 1 stage without worsening of NASH.Resolution of NASH without worsening of fibrosis.

The resolution of NASH is defined as the histopathological disappearance of ballooning and the disappearance or persistence of minimal lobular inflammation (grade 0 or 1) using the NASH CRN scoring system with a type of general lesion that does not qualify as steatohepatitis. Worsening of fibrosis is defined as the progression of at least one stage.

For all the patients, a basal liver biopsy should be obtained prior to the execution of the therapeutic technique and a subsequent biopsy 96 weeks after the procedure should also be obtained.

To avoid inter-observer variability, the histological evaluation will be assessed by two local pathologists independently.

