### Assignment of interventions: allocation

#### Sequence generation {16a}

Randomization will be carried out on all eligible subjects using a computer system. At the randomization visit, eligible subjects will be randomized 1:1 for the following groups:
Experimental group: ESG + lifestyle modificationsControl group: LSG + lifestyle modifications

Randomization will be stratified into 2 strata defined by diabetes status

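### Patients at fibrosis stage 0 may enter the trial and are counted in the primary analysis, but they cannot meet its fibrosis-improvement criterion

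*Protocol article*

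**What the plan says.** All references are to the protocol article.

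- **Inclusion criteria.** The only general limit on fibrosis is an upper one: "Degree of fibrosis < 4 according to the NASH CRN staging system". A further rule covers the low end: "For patients with fibrosis ≤ 1, at least one of the following characteristics must be associated". The characteristics listed are metabolic syndrome, type 2 diabetes or HOMA-IR above 6. Every entrant also needs a NAS of at least 4 with at least 1 point on each component.
- **Primary outcome.** Two histological criteria at week 96 are listed: "Improvement of fibrosis in at least 1 stage without worsening of NASH" and "Resolution of NASH without worsening of fibrosis". The text does not say whether they are co-primary, both required, or alternatives.
- **Secondary outcomes.** Resolution of fibrosis is listed without a denominator.
- **Statistical methods {20a}.** Both primary criteria are assigned to the intention-to-treat population, "so all randomized subjects will be included in the primary analysis".
- **Sequence generation {16a}.** "Randomization will be stratified into 2 strata defined by diabetes status". Fibrosis stage is not a stratification factor.
- **Sample size {14}.** 30 patients, "15 per treatment arm".

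**The concern.** A patient who enters at stage 0 has probability zero of dropping a stage, in either arm. Under the stated analysis set that patient is nevertheless a non-responder on the fibrosis criterion. This has three consequences.

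1. The response rate in each arm is capped at one minus the stage-0 share, and the absolute difference between arms shrinks by the same factor. The trial's hypothesis is that the endoscopic procedure does at least as well as surgery. Failures common to both arms make the arms look more alike, so the dilution is not a safely conservative error.
2. With 15 per arm and no stratification by stage, an uneven split of stage-0 patients adds noise to the comparison.
3. For the secondary outcome of fibrosis resolution, the article does not say whether a stage-0 patient is a success, a failure or not evaluable.

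**Working it through.** **The plan's own figure.** The unpooled two-proportion formula with 85% vs 25%, two-sided alpha 0.01 and 90% power gives

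n = (2.576 + 1.282)² × (0.85×0.15 + 0.25×0.75) / 0.60² = 13.02, so 14 per arm.

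With 7% loss, 14 × 1.07 = 14.98, so 15 per arm and 30 in total. The stated size reproduces. (Dividing 14 by 0.93 gives 15.05, so 16 per arm.) Both planning rates are NASH-resolution rates. The fibrosis criterion has no sample-size basis in the article.

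**Inputs for the fibrosis criterion.**

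- Stage-0 share f: not given. Taken as 10% to 30%, with 20% as the worked case.
- Surgery arm at stage 1 or higher: 65.5%, the only fibrosis-improvement figure in the article (Introduction, meta-analysis of bariatric surgery).
- Endoscopic arm at stage 1 or higher: 25%, purely illustrative. The article gives no such rate.
- 15 per arm, two-sided 0.05 (Statistical methods {20a}), no losses.

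**Dilution.** Each arm's rate is p × (1 − f), so the difference is 0.405 × (1 − f). Power is for the uncorrected chi-square test, by exact enumeration.

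| f | Surgery | Endoscopy | Difference (points) | Power, all 30 |
|---|---|---|---|---|
| 0 | 65.5% | 25.0% | 40.5 | 61% |
| 10% | 59.0% | 22.5% | 36.5 | 54% |
| 20% | 52.4% | 20.0% | 32.4 | 47% |
| 30% | 45.9% | 17.5% | 28.4 | 40% |

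**Restricting to stage 1 or higher, f = 20%.** The 40.5-point difference is kept, with an expected 15 × 0.8 = 12 per arm. Letting each arm's count vary as a binomial (15, 0.8) and averaging the exact power gives 54%, against 47% in all 30. A normal approximation at exactly 12 per arm gives 51% against 45%. The direction is the same, with a gain of about 6 to 7 points.

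**Chance imbalance.** If one arm has 3 more stage-0 patients than the other, the expected difference moves by (3/15) × 65.5% = 13.1 points when both arms respond at 65.5%. At a 25% response rate the shift is 5 points. At f = 20%, the probability of an imbalance of 3 or more is 0.25 if each arm's count is binomial. It is 0.17 if exactly 6 of the 30 are at stage 0.

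**The case against.** **The trial's main target is NASH resolution.** The Objective, Trial design {8} and Sample size {14} all rest on it. Every entrant has at least 1 point for ballooning, so a stage-0 patient can meet that criterion in full. A reader might infer that stage-0 patients are bound to fail the whole primary outcome. The documents do not support that. It would be true only if both criteria were required; if either suffices, these patients lose one of two routes to success. This part of the objection stands and limits the point to the fibrosis endpoints.

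**The size rests on assumptions.** The stage-0 share is unknown. The 65.5% is quoted without a denominator, so it may already include patients without fibrosis. The 25% is illustrative, and a deficit of that size runs against the trial's own hypothesis. This also stands: the factor (1 − f) is exact, but the points and powers are examples.

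**The power gain can be overstated.** Fixing exactly 12 per arm gives 58%, but exact chi-square power jumps with n (12 per arm 0.576, 13 per arm 0.639, 14 per arm 0.564). At 12 per arm the test also exceeds its nominal level, with actual size 0.059 to 0.064 for common rates of 40% to 50%. The averaged 54% is the fairer figure.

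**Imbalance is not bias.** A reader might infer that the design favours one arm, or that 3 extra stage-0 patients move the result by 20 points. Stage-0 failures arise in both arms and the allocation is random, so no systematic bias is shown. Twenty points (3/15) would require every other patient to respond.

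**The analysis plan could settle it.** This is weak. The article fixes the primary analysis set itself. The only population detail it defers is the list of per-protocol exclusions.

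**Conclusion.** The point holds for the fibrosis endpoints. Eligibility admits stage 0, the primary fibrosis criterion cannot be met from stage 0, and the stated analysis set counts these patients as non-responders. The absolute arm difference on that criterion is multiplied by (1 − f). At an assumed 20% share and illustrative rates of 65.5% and 25%, it falls from 40.5 to 32.4 points, and power is 47% in all 30 against about 54% in the stage-1-or-higher subset. An imbalance of 3 stage-0 patients shifts the expected difference by about 13 points at a 65.5% response rate; this is noise, not bias.

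The effect is zero if no stage-0 patient enrols. Its reach into the primary outcome as a whole depends on a combination rule that the article does not state. Power is low on either denominator, so restricting the set corrects the definition but does not rescue the endpoint. The change is worth making, but it does not threaten the NASH-resolution comparison.

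**What to change.** 1. State how the two primary criteria combine, preferably that they are tested separately.
2. If they are separate, analyse fibrosis improvement without worsening of NASH, and the secondary resolution of fibrosis, in all randomised patients with baseline stage 1 or higher. Report the all-randomised version as a supplement. Stage is measured before randomisation, so the comparison remains a randomised one.
3. Keep NASH resolution without worsening of fibrosis on all randomised patients.
4. If the criteria are instead a composite, different denominators do not work. Keep one denominator for the composite and report its fibrosis component in the stage-1-or-higher subset.

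The cost is a few sentences in the outcome and analysis sections, including the combination rule, and a smaller denominator for the fibrosis endpoints. Eligibility is unchanged.
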